# Recovering arm function in chronic stroke patients using combined anodal HD-tDCS and virtual reality therapy (ReArm): a study protocol for a randomized controlled trial

**DOI:** 10.1186/s13063-021-05689-5

**Published:** 2021-10-26

**Keywords:** HD-tDCS, Upper limb function, Virtual reality therapy, Stroke, Rehabilitation, Laterality index, Monitoring, Upper limb use, Cortical activation

## Abstract

**Background:**

After a stroke, 80% of the chronic patients have difficulties to use their paretic upper limb (UL) in activities of daily life (ADL) even after rehabilitation. Virtual reality therapy (VRT) and anodal transcranial direct current stimulation (tDCS) are two innovative methods that have shown independently to positively impact functional recovery of the paretic UL when combined with conventional therapy. The objective of the project will be to evaluate the impact of adding anodal high-definition (HD)-tDCS during an intensive 3-week UL VRT and conventional therapy program on paretic UL function in chronic stroke.

**Methods:**

The ReArm project is a quadruple-blinded, randomized, sham-controlled, bi-centre, two-arm parallel, and interventional study design. Fifty-eight chronic (> 3 months) stroke patients will be recruited from the Montpellier and Nimes University Hospitals. Patients will follow a standard 3-week in-patient rehabilitation program, which includes 13 days of VRT (Armeo Spring, 1 × 30 min session/day) and conventional therapy (3 × 30 min sessions/day). Twenty-nine patients will receive real stimulation (4x1 anodal HD-tDCS montage, 2 mA, 20 min) to the ipsilesional primary motor cortex during the VRT session and the other 29 patients will receive active sham stimulation (2 mA, 30 s). All outcome measures will be assessed at baseline, at the end of rehabilitation and again 3 months later. The primary outcome measure will be the wolf motor function test. Secondary outcomes will include measures of UL function (Box and Block Test), impairment (Fugl Meyer Upper Extremity), compensation (Proximal Arm Non-Use), ADL (Actimetry, Barthel Index). Other/exploratory outcomes will include pain, fatigue, effort and performance, kinematics, and motor cortical region activation during functional motor tasks.

**Discussion:**

This will be the first trial to determine the impact of adding HD-tDCS during UL VRT and conventional therapy in chronic stroke patients. We hypothesize that improvements in UL function will be greater and longer-lasting with real stimulation than in those receiving sham.

**Trial registration:**

The ReArm project was approved by The French Research Ethics Committee, (Comité de Protection des Personnes-CPP SUD-EST II, N°ID-RCB: 2019-A00506-51, http://www.cppsudest2.fr/). The ReArm project was registered on ClinicalTrials.gov (NCT04291573, 2^nd^ March 2020.

**Supplementary Information:**

The online version contains supplementary material available at 10.1186/s13063-021-05689-5.

## Background

With a very high prevalence, stroke is the second cause of death and the first cause of acquired disability in adults in well-developed countries. Stroke frequently leads to sensory-motor and functional physical limitations [32]. It is also responsible of 2 to 4% of total expenses in health care with a need of developing new re-educative treatments [32]. Hemiparesis is one of the most common disabilities caused by stroke. Poor recovery of the paretic UL function affects more than 80% of stroke survivors [26] and is mostly persistent 3 months post-stroke, in the late sub-acute and chronic stages, even after intensive rehabilitation [54]. Although, repetitive motor training appears to be efficient for improving paretic UL function [73], there is no standardized protocol for the rehabilitation of the paretic UL after stroke [60]. The lack of recovery often results in non-use of the paretic UL [68], leading to reorganization of brain functional networks [48] and finally restricting use dependent functional recovery [50].

Stroke leads to spontaneous reorganization of the central nervous system corresponding to neural plasticity [34]. Spontaneous recovery and regeneration mechanisms of brain reorganization are triggered soon after a brain lesion. Over time, from late sub-acute stage to chronic stage of stroke, there is less and less spontaneous plasticity and it is more difficult to recover paretic UL function [34]. During the late sub-acute and chronic stages after a stroke, experience-dependent plasticity takes on a greater role for functional recovery of the paretic UL [37]. Some aspects of the rehabilitation program (e.g., intensity and volume of practice, variety, specificity, motivation, and biofeedback) can modulate this experience-dependent plasticity [38, 65]. In this context, virtual reality therapy (VRT) that combines rehabilitation exercises with gaming elements appears to be a well-suited intervention in promoting functional recovery of the paretic UL [45].

VRT can be defined as the use of a brain-computer interaction method [70] for providing patients multimodal sensory and motor stimuli with the help of immersive environment workspaces. Herein, VRT allows a simulated practice of functional motor tasks with more repetitions than in conventional therapy used in post-stroke rehabilitation [19, 40, 70]. Furthermore, VRT can limit fatigue and loss of enthusiasm and improve patient cooperation and engagement, which can positively influence recovery of the paretic UL [42, 43, 67]. As such, biofeedback provided to the patient during VRT was shown to improve the activation of the lesioned hemisphere, fostering a better relearning of motor tasks [33]. A recent Cochrane review [45] indicated that VRT is equally effective in improving paretic UL function compared to conventional therapy (low-quality evidence); however, there was some evidence that VRT resulted in a slightly better ability to manage ADL such as showering and dressing (moderate-quality evidence). Moreover, when combined with a conventional therapy rehabilitation program post-stroke, VRT more efficiently improves paretic UL function and patient’s capability to succeed in ADL [41, 45]. Among the VRT methods available, robot-assisted VRT systems use an exoskeleton providing assistive control of the paretic UL (e.g., through counter-gravity springs, such as Armeo system) and thus allows longer training sessions with reduced fatigue [49]. Accordingly, robot-assisted VRT has been shown to achieve greater and long-lasting improvements in paretic UL function in comparison to conventional therapy alone [69].

Enhancing recovery of paretic UL function after stroke can also result from non-invasive brain stimulation (NIBS) through modulation of motor cortical excitability. NIBS has the ability to modulate neural excitability and generate new neuronal associations inducing in turn brain plasticity [62]. Among NIBS techniques, transcranial direct current stimulation (tDCS), which applies low currents around 1–2 mA during 10 to 30 min for single or multiple sessions [10, 15] is a promising clinical potential that can be easily added onto an UL rehabilitation protocol. Moreover, its active sham mode enabling randomized clinical trials allows to apply brief stimulation (10–90 s) while the patient is receiving a rehabilitation treatment that provides the same scalp sensations as a real stimulation session [61, 63]. By increasing ipsilesional motor cortical excitability and promoting neuroplasticity, anodal tDCS added to motor task training has been shown to improve functional recovery of the paretic UL after a stroke [1, 23–25, 70]. Allman et al. [1] reported long-term (3 months) improvements in functional paretic UL clinical assessments (Wolf Motor Function Test (WMFT), Action Research Arm Test (ARAT)) in chronic stroke patients (> 6 months) with ipsilesional anodal tDCS added to daily hand and arm motor rehabilitation training over 2 weeks (9 × 1-h sessions) compared to sham stimulation. This study also showed an increased movement related cortical activation and grey matter volume in ipsilesional motor cortical regions for patients in the stimulation group compared to sham. Figlewski et al. [23] applied anodal tDCS to the ipsilesional motor cortex during constraint-induced therapy in chronic stage stroke patients (3–36 months) over 2 weeks (9 × 6-h sessions) and found greater improvements in paretic UL function (WMFT) when compared with constraint-induced therapy alone. A recent Cochrane review [22] indicated the effectiveness of tDCS versus sham for improving ADL outcomes after stroke (low to moderate quality evidence). Altogether, these studies provide clinical support that adding anodal tDCS to a rehabilitation program may bolster more the recovery of paretic UL function and ADL in chronic stroke patients. Indeed, anodal tDCS might facilitate activity-dependent plasticity within the neural networks recruited already within a rehabilitation treatment, thereby contributing to greater and sustainable clinical gains [1, 11, 23].

The two aforementioned adjunct stroke rehabilitation methods (VRT and anodal tDCS), used separately as a complement to conventional rehabilitation are expected to improve and maintain recovery of the paretic UL by positively impacting neuroplasticity. Thus, to enhance the effect of conventional therapy, adding anodal tDCS during VRT could be more efficient than when VRT is used alone [66, 70]. However, there is a paucity of studies that have evaluated the effectiveness of this VRT and anodal tDCS combination in post-stroke rehabilitation. Triccas et al. [71] investigated the effects of adding anodal tDCS (ipsilesional motor cortex, 1 mA, 20 min) to an 8-week robot-assisted VRT (Armeo spring exoskeleton) rehabilitation program (18 × 1-h sessions) for early sub-acute (2–3 months) and chronic (9–61 months) stroke patients. Although the addition of anodal tDCS to VRT was well tolerated, there were no added clinical benefits (Fugl-Meyer Assessment, ARAT, Motor Activity Log (MAL), Stroke Impact Scale (SIS)) of such a combination. The authors considered that the low number of sessions of VRT per week (2–3 sessions) and the small/heterogenous group of patients per group (*n* = 11) might have reduced the chances of detecting a clinical difference between groups. Moreover, the standard anodal tDCS montage used could prevent significant changes of excitability within the target brain regions. Improving the focality of tDCS effects over sensorimotor regions with anodal high definition (HD)-tDCS was found to induce a greater increase in cortical excitability [39] and haemodynamic activity [55] comparatively to conventional tDCS montage in healthy subjects and thus, might induce a greater neuroplasticity stimulus. Chhatbar et al. [17] reported from a meta-analysis of tDCS UL motor recovery studies a dose–response relationship with electrode size and current density, such that a higher current density or smaller electrode size being associated with greater efficacy on paretic UL motor recovery (Fugl Meyer Upper Extremity (FM-UE)) in chronic stroke. Therefore, it can be expected that applying a more intensive anodal HD-tDCS (2 mA, 20 min) and VRT program (3 weeks, 13 × 30-min sessions) will provide greater clinical benefit [21].

The ReArm project is a randomized-control trial of late subacute and chronic stroke patients (> 3 months) designed to determine the impact of adding anodal HD-tDCS (2 mA, 20 min, ipsilesional motor cortex), compared to sham, during an intensive 3-week UL VRT program (13 × 30-min sessions) supplementing a conventional therapy program (39 × 30-min sessions). The primary objective will be to evaluate the impact of this intervention the on paretic UL function 3 months after the end of the rehabilitation. Secondary and exploratory objectives will be to investigate the evolution of the paretic UL use in ADL, performance, kinematics, and movement-related activation of motor cortical regions during functional motor tasks, from the beginning to the end of the 3-week program and after 3 months. We hypothesize that adding anodal HD-tDCS during VRT, as a supplement to conventional therapy rehabilitation program, will result in greater retention of clinical benefits 3 months after the intervention and increased use and functional recovery of the paretic UL.

## Methods

### Ethics

The study was approved by the National Research Ethical Committee (Comité de Protection des Personnes-CPP SUD-EST II, No. ID-RCB 2019-A00506-51, http://www.cppsudest2.fr/) and is registered on http://www.clinicaltrials.gov (NCT number, NCT04291573).

### Participants

Fifty-eight adult hemiparetic stroke patients will be recruited (see “Sample size” section for details).

#### Inclusion criteria

Inclusion criteria will be patients (1) aged between 18 and 90 years old, (2) at more than 3 months of a first cerebrovascular accident of any aetiology (haemorrhagic or ischaemic), and (3) with UL motor impairment (FM-UE ≥ 15 [27]).

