#### Randomization

The Capture System software (Ennov Clinical, module randomization, Paris, France) will be set up by the randomization administrator, from the Innovation and Research Department of the Hospital, to give a blinding code to each patient. A centralized randomization will be performed using the Capture System software (Ennov Clinical, module randomization, Paris, France). A minimization algorithm will assure the balance of groups regarding PRM centres (CHU Montpellier or Nimes) and stroke severity (FM-UE score lower or higher than 40 [72]); see “Blinding of group and stimulation protocols” section for more details. For each inclusion, another hospital department, the clinical investigation centre, will use the software to allocate the right protocol.

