### Clinical data and outcome measures

#### Clinical data

Clinical data will be collected by the medical doctor during the routine clinical visit, including date of birth, age, sex, hand laterality before and after the stroke, date of the stroke, delay from the stroke to the inclusion, and characteristic of the brain lesion (type and location). Treatment, medication, and health events will also be reported. The source documents are the original data, sheets, and files, from which the data concerning the research are copied in the electronic case report form (eCRF) by the clinical investigation centre (CIC).

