## Discussion

The aim of the ReArm project is to evaluate the additional effects on paretic UL function by including anodal HD-tDCS during a 3-week intensive VRT program to supplement conventional therapy in late subacute and chronic stroke patients.

VRT and conventional therapy are equally effective in improving paretic UL function in stroke patients [45]; however, VRT is less labour intensive from a physiotherapy and occupational therapy perspective for the same clinical gains. So therapists can focus on other aspects of rehabilitation as such as providing encouragement, directions, and observing the quality of movement. As such, the PRM departments of Montpellier and Nimes University Hospitals have integrated VRT sessions into conventional therapy sessions as a standard in-patient stroke rehabilitation program. Anodal HD-tDCS is as a relatively simple and easily applied NIBS technique that has been shown to enhance motor cortical excitability and plasticity. Anodal HD-tDCS is an ideal candidate to help boost re-learning of paretic UL function in chronic stroke patients. Accordingly, combining anodal HD-tDCS with VRT rehabilitation could further improve neuroplastic effects induced by VRT alone and lead to greater and sustainable clinical gains [11].

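### One entry window of more than 3 months carries two population labels, and time since stroke is left out of both the minimisation and the stated primary test (minor)

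*Protocol article*

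**What the plan says.** **Who enters.** Inclusion criterion 2 admits patients "at more than 3 months of a first cerebrovascular accident of any aetiology (haemorrhagic or ischaemic"). There is no upper limit on time since stroke.

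**What they are called.** The abstract's Methods says "Fifty-eight chronic (> 3 months) stroke patients will be recruited". The end of the Background describes a "randomized-control trial of late subacute and chronic stroke patients (> 3 months"), and the Discussion's aim is to "supplement conventional therapy in late subacute and chronic stroke patients". The title, the Sample size section and the impact statement late in the Discussion mention chronic patients only.

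**What the protocol says about stage.** The Background says that "from late sub-acute stage to chronic stage of stroke, there is less and less spontaneous plasticity", and that arm function becomes harder to recover.

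**What is done with time since stroke.** The Clinical data section records "delay from the stroke to the inclusion". The Randomization section minimises for "balance of groups regarding PRM centres (CHU Montpellier or Nimes) and stroke severity (FM-UE score lower or higher than 40") and nothing else. Under Primary outcome measure analysis, the V3 comparison is a two-group t-test or a rank test, with no covariate.

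**Planning source.** The WMFT study cited with d = 0.4 is described in the Background as having been done "in chronic stroke patients (> 6 months) with ipsilesional anodal tDCS added to daily hand and arm motor rehabilitation training".

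**The concern.** The protocol identifies stage after stroke as related to recovery, and then neither balances it nor adjusts for it. A patient who enters just after 3 months is assessed at V2 on day 19 and at V3 three months later. That patient reaches V3 between 6 and 7 months after the stroke, having spent most of the trial in the period the protocol calls late sub-acute. A patient ten years out enters under the same criterion.

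Two things are at stake. The first is precision and credibility. With 29 per arm, one arm could by chance hold more of the recently affected patients, and the stated test would not account for it. The second is the claim. If the result is reported for chronic stroke, as the title and impact statement suggest, a reader cannot tell how far it rests on patients at 3–6 months.

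**Working it through.** **1. The plan's own figure.** Inputs from the Sample size section: d = 0.8, two-sided 5%, power 80%, 10% loss. A two-sample t-test needs 25.5, so 26 per group, with 80.7% power at 26. Then 52 / 0.9 = 57.8, so 58. Both stated figures reproduce.

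**2. Chance imbalance.** The documents do not give the share of patients at 3–6 months, so it is assumed. If k of 58 are in that window and 29 go to each arm, the number in one arm is hypergeometric (58, k, 29). This treats minimisation on the other two factors as uninformative about time since stroke.

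| k of 58 | P(arms differ by 5 or more such patients) |
|---|---|
| 6 | 2% |
| 12 | 10% |
| 17 | 25% |
| 23 | 28% |

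These probabilities are two-sided; half of each favours the active arm. Five patients is 5/29 = 17 percentage points. If the extra gain at 3–6 months were 0.5 to 1.0 SD (assumed), the observed arm difference in that allocation could be shifted by chance by 0.172 × 0.5 = 0.09 to 0.172 × 1.0 = 0.17 SD. For scale, the standard error of the arm difference at 26 per arm is √(2/26) = 0.28 SD.

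**3. Bias and type I error.** The unadjusted t-test was simulated with 26 per arm and 40,000 runs per setting, for shares of 20–50% and extra gains of 0.3–0.8 SD. The mean bias was zero to within simulation error, and type I error was 4.8–5.1%.

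**4. Power.** Let q be the share at 3–6 months and g the extra gain, in units of the SD within stage. Leaving stage out inflates the variance by 1 + g²q(1 − q), so the effective d is 0.8 / √(1 + g²q(1 − q)). For example, with q = 0.3 and g = 1.0, d = 0.8 / √1.21 = 0.727. Power at 26 per arm:

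| q | g = 0.3 | g = 0.5 | g = 0.8 | g = 1.0 |
|---|---|---|---|---|
| 0.2 | 80% | 79% | 77% | 75% |
| 0.3 | 80% | 79% | 76% | 73% |
| 0.5 | 80% | 78% | 75% | 72% |

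Simulation agrees to within about half a point. The range is therefore roughly 73–80%, with only the most extreme cell at 72%.

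**5. Which remedy recovers the loss.** The same simulation (26 per arm, 40,000 runs) was run with exact balance on stage, with covariate adjustment, and with both. At q = 0.3:

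| | g = 0.5 | g = 1.0 |
|---|---|---|
| As planned | 79.0% | 73.1% |
| Balanced, unadjusted t-test | 79.5% | 74.6% |
| Not balanced, adjusted | 80.2% | 80.0% |
| Balanced and adjusted | 81.0% | 80.9% |

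Balancing alone gains about 1 point, because the spread between stages stays in the t-test's error term. Adjustment gains about 1 to 7 points.

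**The case against.** Much of the opposing case stands, and it rules out several stronger readings.

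- **That the comparison is biased.** A reader might infer this from the missing balance. Allocation is random, the expected imbalance is zero and the test keeps its 5% level. Any shift belongs to a particular allocation and is already part of sampling error.
- **That a large imbalance is likely.** The 25–28% figures need an assumed share of about 30–40%. At 10% of patients the figure is 2%. A 1.0 SD extra gain would exceed the whole planned effect of 0.8, and no passage supports it.
- **That the wider window is hidden.** It is disclosed in the abstract, the Background and the Discussion. The Background also calls 3–36 months chronic stage in another cited WMFT trial, and says experience-dependent plasticity matters more in both stages. The 3-month cut has a stated rationale; 6 months is one cited study's boundary.
- **That the sample size fails because its source enrolled beyond 6 months.** The planned d = 0.8 was not taken from that study's 0.4. The protocol raised it on current density and number of sessions. Any effect of the entry window on d cannot be computed from the documents.
- **That the cited trial combining tDCS with the same exoskeleton shows the harm.** It mixed early sub-acute patients (2–3 months) with chronic ones, at 11 per group. The present criterion excludes that early group.

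Minimising on centre and severity is a reasonable choice for 58 patients, and a separate estimate beyond 6 months could sit in an analysis plan that is not shown. None of this removes the conflicting labels. Nor does it change the fact that the protocol itself specifies an unadjusted test.

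**Conclusion.** The point holds as a minor one. The same population has two names, and the narrower one appears where the result will be claimed. A factor that the protocol links to recovery, and already records, is used in neither the allocation nor the stated V3 test.

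The statistical cost is lost precision: power at d = 0.8 of roughly 73–80% instead of 81%. This rests on an assumed share of 20–50% at 3–6 months, an assumed extra gain of 0.3–1.0 SD, and reading 0.8 as standardised by the within-stage SD. If 0.8 already refers to the SD of the mixed population, planned power stays at 81% and adjustment is a gain on top. The cost in interpretation cannot be put in numbers: a pooled effect does not by itself show benefit in chronic patients alone.

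**What to change.** 1. Use one description, late sub-acute and chronic (> 3 months), in the title, abstract, sample-size rationale and conclusions. In the rationale, note that the cited WMFT study covered only patients beyond 6 months.
2. Include time since stroke as a pre-specified covariate in the V3 WMFT analysis. This recovers most of the lost precision.
3. Add time since stroke, for example up to 6 months versus more than 6 months, to the existing minimisation. Without the covariate this step gains little.
4. Optionally, pre-specify a supportive V3 estimate in patients beyond 6 months. It would be imprecise at this sample size.

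The cost is wording changes, one more factor in the central software, one degree of freedom, and slightly looser balance on centre and FM-UE. The sample size of 58, the entry criteria and data collection are unchanged.
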